## LIST OF ABBREVIATIONS AND RELEVANT DEFINITIONS

| Abbr.                 | Dutch                                             | English                                       |
|-----------------------|---------------------------------------------------|-----------------------------------------------|
| CO2 | Koolstofdioxide                                   | Carbon Dioxide                                |
| KNO            | Keel, neus, oor                                   | Ear, Nose, Throat                             |
| METC           | Medisch Ethische Toetsing Commissie               | Medical Research Ethics Committee             |
| POK            | Poliklinische operatiekamer                       | Outpatient surgery room                       |
| (S)AE          | (Serious) Adverse Event                           | (Serious) Adverse Event                       |
| TE             | Tonsillectomie                                    | Tonsillectomy                                 |
| TO             | Tonsillotomie                                     | Tonsillotomy                                  |
| VAS            | Visual Analogue Scale                             | Visual Analogue Scale                         |
| WMO            | Wet Medisch-wetenschappelijk onderzoek met mensen | Medical Research Involving Human Subjects Act |

## 1. Summary

**Background:** In adults, a tonsillectomy can be performed for tonsil-related complaints according to the classic dissection technique under anesthesia. This procedure is associated with considerable morbidity. Outpatient CO2 laser tonsillotomy under local anesthesia appears to be an interesting alternative for a selected group of adults.

**Objective:** To evaluate the added value of CO2 laser tonsillotomy for the treatment of tonsil-related complaints.

**Study design:** The study will be conducted as an open multicenter randomized controlled trial. The patient will draw lots for a classic tonsillectomy or a laser tonsillotomy after informed consent.

**Study population:** Patients older than 18 years with tonsil-related complaints for which surgical intervention is indicated.

**Intervention:** A group will undergo a classic tonsillectomy under anesthesia. The other group will undergo a CO2 laser tonsillotomy under local anesthesia.

**Outcome measures:**

The results will be based on the following outcome measures: number of days postoperative recovery to resumption of daily activities, presence or absence of preoperative tonsil-related complaints, postoperative pain scores and analgesia use, procedure-related complications and patient satisfaction.

**Risks and complications:** For the number of clinic visits, measurement moments and actions, see the flow chart in chapter 3.

**Complications of laser treatment:**

- About 10% have not gotten rid of the complaints and have so many complaints that they undergo a classic dissection tonsillectomy
- In total, about 20% of patients undergo more than 1 laser treatment
- wound infection (3.4%)
- Bleeding requiring intervention (<1%)
- Allergic reaction to the local anesthetic (<1%)
- Side effects of the anesthetic (xylocaine 2% / adrenaline 1: 80,000) as described in the package insert (<1%)

**Complications of a classic dissection tonsillectomy**

- Bleeding requiring intervention (+ - 1.4%)
- Wound infection (+ - 2%)
- Complications of anesthesia (<1%)

## 2. Introduction

In adults, a tonsillectomy is performed using the classic dissection technique under general anesthesia. This procedure is associated with considerable morbidity. Outpatient CO2 laser tonsillotomy under local anesthesia appears to be an interesting alternative for a selected group of adults. Previous studies on outpatient CO2 laser tonsillotomy show that this procedure is associated with considerably less postoperative morbidity [1-7]. The rationale behind this therapy is that the tonsil crypts are the source of infection [8-9]. In contrast to a classic tonsillectomy, with a laser tonsillotomy, the crypts with the lymphatic tissue in between are superficially vaporized (cryptolysis). The tonsil capsule and peritonsillar space remain unaffected. The latter may explain why there is less (post) bleeding [10, 11, 12] and less pain, while the intended total cryptolysis prevents reinfection [3-7]. Furthermore, there is no need for general anesthesia and hospitalization. In addition to a medical benefit, this can also yield benefits from a financial point of view. An important side note to the available results of previous research is that most of the results are based on small patient groups where the patient characteristics are often lacking [14]. Few prospective follow-up results are known. For this reason, we conducted a follow-up study with the aim of looking at the feasibility, effectiveness and complications of a CO2 laser tonsillotomy[15].

In a period of four and a half years, 425 patients with chronic recurrent tonsillitis, fetor ex ore, swallowing complaints or obstructive complaints due to tonsil hypertrophy underwent a CO2 laser tonsillotomy after informed consent. This showed that patients were able to resume their daily activities and work after an average of 4.2 days. Of the 204 patients who could be followed for a long time (mean 16.8 months, range 1-40) it turned out that 69.6% eventually became completely free of complaints, in 19.1% there was such a reduction in complaints that no further intervention was desired, 10.3% were not free of symptoms after treatment and underwent a classic tonsillectomy. In 2.6% there was minimal bleeding which could be treated conservatively. In 8.6% antibiotics were prescribed shortly after the procedure, but these figures do not fully correspond to reality. In the early years, the GP regularly prescribed antibiotics because of the white discoloration of the wound bed. After better information provision, this number has decreased significantly. In 2010, 117 patients were treated with the laser and antibiotics were prescribed for a wound infection in 4 patients (3.4%). Two patients had a severe vagal reaction to the local anesthetic, causing the procedure to be prematurely discontinued.

A comparison with the classic tonsillectomy was not made in this study. Because of the expected potential of the CO2 laser tonsillotomy, we feel the need to perform a thorough comparative study with the classic tonsillectomy. The aim of this study is to provide more insight into postoperative recovery, effectiveness, complications (both in the short and longer term) and patient satisfaction after CO2 laser tonsillotomy compared to a classic tonsillotomy.

### 3. Aim of the study

The aim of this study is to compare the effectiveness of CO2 laser tonsillotomy in a selected group of patients with a classic tonsillectomy. It is hypothesized that the number of days postoperative recovery after the laser procedure differs for at least 3 days from the classic tonsillectomy, that the effectiveness of the CO2 laser tonsillotomy does not differ by more than 30% from the classic tonsillectomy and there are significantly better secondary outcomes.

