##### 3.1.2. Secondary outcome measures

- Presence or absence of the tonsil related complaint
- Number of episodes of tonsillitis per year objectified by the general practitioner or ENT specialist
- Number of antibiotics courses for tonsillitis each year
- Average number of days per year of sick leave due to tonsil-related complaints
- Presence / absence of halitosis
- Presence / absence of detritus
- Pain complaints during / after the procedure
- Complications
- Patient satisfaction with regard to the procedure and reduction of complaints (using VAS)
- Time to return to work / school resumption
- Number of days of sick leave in the year after surgery (second follow-up study)
- Cost Effectiveness laser tonsillotomy vs classic tonsillectomy (second follow-up study)
- Budget Impact laser tonsillotomy vs classic tonsillectomy (second follow-up study)

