### 7.4. Sample size calculation

Using data from a previous non-randomized prospective study our group conducted a sample size calculation prior to conducting the present the randomized controlled trial. A two-sided log-rank test with an overall sample size of 190 subjects (95 in the TE group and 95 in the TO group) achieves 80.2% power at a 0.05 significance level to detect a TO median recovery time of 8 days when the TE group median survival time is 13.5 days within a 14-day total observation time.

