**The variables to assess effectiveness and patient satisfaction include the following:**

- Presence / absence of the complaints for which the intervention was undergone
- Duration of recovery period (time to return to work / resumption of daily activities) in days
- Duration of use of painkillers in number of days
- Satisfaction with the procedure (VAS score)
- Complaints after surgery (on / absent, VAS score)
- Short and long term complications (bleeding, infection, abscess)
- Number of laser sessions required
- If patient eventually underwent classic tonsillectomy
- Number of antibiotics used in the period after surgery in connection with tonsil-related complaint
- Number of days of absenteeism from work / school related to tonsil-related complaints after the procedure
- The patient would / would not recommend the procedure to others

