## 8.2. Analysis

All analyzes will be performed with an intention-to-treat analysis.

A two sided p value  $<0.05$  will be considered significant for all analyses. Survival analysis will be used to compare the primary outcome of recovery time. Survival analysis will also be used to compare time to return to work and postoperative analgesic use. Secondary outcome measures on a continuous scale will be compared using unpaired T-tests or Mann-Whitney U tests, depending on the normality of data (tested using Shapiro-Wilk test). Proportions will be compared using Fisher exact tests.

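### The protocol states effectiveness as a within-30% hypothesis, but its only planned test of proportions is a Fisher test of no difference, and no analysis uses the 30%

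*Protocol*

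**What the plan says.** Section 3 of the protocol gives three hypotheses. The second is "that the effectiveness of the CO2 laser tonsillotomy does not differ by more than 30% from the classic tonsillectomy". It does not say whether the 30% is absolute or relative. As worded it runs in both directions.

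The protocol never equates effectiveness with a single variable, but the natural one is binary. Section 3.1.2 opens its secondary outcomes with "Presence or absence of the tonsil related complaint", and the list of effectiveness and satisfaction variables in section 8.1 opens with "Presence / absence of the complaints for which the intervention was undergone".

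Section 8.2 fixes the analysis: "Proportions will be compared using Fisher exact tests". It sets a two-sided p<0.05 that "will be considered significant for all analyses", and adds: "All analyzes will be performed with an intention-to-treat analysis". The 30% does not reappear there or anywhere else in the protocol, and no confidence interval, non-inferiority test or equivalence test is tied to it.

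Section 7.4 sizes the trial on recovery time alone, with an "overall sample size of 190 subjects (95 in the TE group and 95 in the TO group").

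**The concern.** A claim that two treatments differ by no more than a margin has to be judged against that margin. Fisher's test asks whether the difference is zero. A difference can be clearly non-zero and still clearly smaller than 30 points. It can also fail to reach significance because few patients were followed, without being shown to be small.

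The case for the laser procedure has two legs: faster recovery, and an acceptable loss of effectiveness if there is any. The second leg has a stated hypothesis but no matching analysis. If only a Fisher p-value is reported, p<0.05 is likely to be taken as a failure of that leg even when the data support it. If a margin rule is added once the data are known, it will look chosen to suit them.

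This goes beyond detail left to an analysis plan. The protocol names both the hypothesis and the test, and the two do not match.

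**Working it through.** **Inputs.** 95 per arm (section 7.4). Margin 30%, read here as percentage points (section 3; scale not stated). Two-sided 0.05 and Fisher exact (section 8.2). Laser success in the earlier uncontrolled series: 69.6% complaint-free, plus 19.1% improved enough to want nothing further, so 69.6 + 19.1 = 88.7% (section 2). Tonsillectomy success is not given; 85% to 95% is assumed. The other laser rates are assumptions too.

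**The plan's own figure.** The only sizing figure is 80.2% power for the log-rank test. With exponential times, the hazard ratio is 8/13.5 = 0.593. Expected events are 95 × [(1 − 2^(−14/13.5)) + (1 − 2^(−14/8))] = 95 × (0.513 + 0.703) = 115.5. Schoenfeld power is Φ(√115.5/2 × |ln 0.593| − 1.96) = Φ(0.85) = 80.3%; simulation gives 80.2%. The figure reproduces. It says nothing about effectiveness.

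**Fisher against the margin.** For each pair of true rates, the binomial probabilities of all 95-vs-95 tables were summed over three sets: Fisher p<0.05; Newcombe 95% interval for the difference wholly within ±30 points; and both at once.

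| Tonsillectomy vs laser | Gap (points) | Fisher significant | Interval inside ±30 | Both at once |
|---|---|---|---|---|
| 85% vs 75% | 10 | 35% | 94% | 28% |
| 90% vs 75% | 15 | 74% | 79% | 53% |
| 95% vs 80% | 15 | 86% | 87% | 73% |
| 95% vs 75% | 20 | 97% | 50% | 48% |
| 90% vs 69.6% | 20.4 | 93% | 41% | 34% |
| 90% vs 88.7% | 1.3 | 3.5% | over 99.9% | 3.5% |

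The hypothesis is true in every row. The last column is the chance that the planned test reports a difference while the data support the hypothesis.

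**One table worked.** Take 86/95 vs 71/95.
- Difference: 0.9053 − 0.7474 = 0.158. Fisher p = 0.007.
- Wilson limits: 0.8297 to 0.9494 and 0.6516 to 0.8240.
- Newcombe upper limit: 0.158 + √[(0.9494 − 0.9053)² + (0.7474 − 0.6516)²] = 0.158 + 0.105 = 0.263.
- Newcombe lower limit: 0.158 − √[(0.9053 − 0.8297)² + (0.8240 − 0.7474)²] = 0.158 − 0.108 = 0.050.

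The interval of 5.0 to 26.3 points is inside the margin, yet Fisher is significant.

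**The other direction.** Over all tables with Fisher p≥0.05, the largest upper limit for the difference is:

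| Per arm | Largest upper limit (points) |
|---|---|
| 95 | 28.1 |
| 85 | 29.4 |
| 80 | 30.7 |
| 76 | 31.8 |

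So with everyone evaluable, on the absolute reading, a non-significant result always goes with an interval inside 30 points. The guarantee is lost at 80 per arm, a loss of 15/95 = 16%.

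**Scale.** A relative 30% would be 0.30 × 90 = 27 points at a tonsillectomy rate of 90%, and 0.30 × 95 = 28.5 at 95%.

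**The case against.** Four points can fairly be made for the plan.

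1. *The protocol prescribes no wrong reading.* Section 8.2 says only that proportions are compared. A reader might infer that a significant Fisher result would refute the hypothesis and reverse the trial's conclusion. The document states no such rule, and the result would not formally refute it. This stands: the defect is a missing link between margin and test, with the risk of misreading that follows.

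2. *Non-significance is not empty at the planned size.* A reader might infer that Fisher can never support the claim. That is right as logic, but at 95 per arm no non-significant table has an upper limit above 28.1 points. This also stands, on the absolute reading. The practical error needs incomplete follow-up. That cannot be ruled out with forms sent by e-mail up to 2 years (section 7.5), but the protocol gives no expected loss.

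3. *The size depends on assumed rates.* No tonsillectomy success rate is stated. If success counts improved patients and the true rates are 90% and 88.7%, the conflict almost vanishes. This stands as a limit on the size, not on the mismatch.

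4. *An interval can be added later.* A statistical analysis plan, not shown, may do so. The counts are collected anyway. But an analysis plan that followed section 8.2 as written would carry the mismatch over, and the scale and direction of the 30% belong with the hypothesis.

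**Conclusion.** The point holds in limited form. The protocol states a within-30% hypothesis and plans a test of zero difference, so the planned analysis does not answer the question asked. For true gaps of 10 to 15 points, Fisher is significant while the interval lies inside the margin in 28% to 73% of trials; with nearly equal rates this falls to about 3.5%. These figures assume 95 evaluable patients per arm, an absolute 30-point margin, the complaint-free proportion as the effectiveness measure, and assumed tonsillectomy rates.

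The documents do not support a claim that the trial's main result is at risk. Effectiveness is a secondary outcome, and the log-rank comparison of recovery time and its power are unaffected. Nor would an interval guarantee a favourable answer: at 90% vs 69.6% it falls inside the margin in only 41% of trials, and the trial was not sized for this claim. It should be fixed, before the outcome data are analysed.

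**What to change.** In section 3, state whether the 30% is absolute or relative, and whether the claim is one-directional (laser not worse by more than the margin) or two-directional (equivalence).

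In section 8.2, tie the claim to an estimate: the difference between arms in the proportion free of the presenting complaint at one named time point, with a two-sided 95% confidence interval (Newcombe or Miettinen-Nurminen, for example). Conclude in favour only if the interval respects the margin in the stated direction or directions. If the margin is relative, use an interval on the matching scale. Add a per-protocol sensitivity analysis, because section 8.2 provides for intention-to-treat only and crossover or incomplete treatment can make the arms look alike.

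Fisher's test may stay as a descriptive test of difference and for complications.

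The cost is one paragraph of wording and slightly more analysis, with no extra patients or data.

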### 7.5. Study procedure

To evaluate the primary and secondary outcome measures, the patient will be asked to complete a digital evaluation form preoperatively, 2 weeks, 6 months, 1 year and 2 years after the procedure (follow-up study). These forms will be offered by e-mail. In the event of recurrent complaints after the procedure, the patient is asked to go to the ENT doctor /

general practitioner for assessment and to report this to the investigator (by telephone / email). This will also be re-evaluated in the fixed measurement moments.

The operator will fill in a number of questions related to the procedure.

Laser procedure:

- Duration of the laser procedure
- Total duration of outpatient visit
- Amount of local anesthesia administered (number of cartridges)
- Pain during the procedure (VAS score) (patient perception)
- Use of supplemental anesthetic, and the amount thereof
- Coagulation required / not required during procedure
- Complications during surgery

Classic TE procedure:

- Duration procedure (cutting time)
- Duration of hospitalization
- Pain relief administered during surgery (medication, dosage)
- Pain related to procedure (injecting an IV, etc.) (VAS score) (perception pt)
- Coagulation required / not required during procedure
- Complications during surgery

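### The study hypothesis includes significantly better secondary outcomes without saying which or how many, and the 0.05 criterion covers every analysis, so a chance result could be reported as confirmation

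*Protocol*

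**What the plan says.** Section 3 states a hypothesis in three parts: a difference of at least 3 days in recovery, effectiveness within 30% of classic tonsillectomy, and that "there are significantly better secondary outcomes". The third part gives a direction (better) but no outcome, number or time point.

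Section 8.2 sets the criterion. It starts from "A two sided p value" below 0.05, which "will be considered significant for all analyses". It then assigns survival analysis, t-tests or Mann-Whitney tests to the outcomes according to type, and adds: "Proportions will be compared using Fisher exact tests".

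Section 3.1.2 lists 13 secondary outcomes, repeated in section 7.2. The first is "Presence or absence of the tonsil related complaint". The tenth is "Time to return to work / school resumption". The last three (sick leave in the year after surgery, cost-effectiveness and budget impact) are marked as belonging to a second follow-up study. Section 7.5 collects forms before surgery and "2 weeks, 6 months, 1 year and 2 years after the procedure".

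The protocol gives no ranking of the secondary outcomes, no adjustment for their number and no label calling them supportive or exploratory.

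**The concern.** Secondary outcomes tested at a nominal 0.05 are common and usually harmless, because nothing confirmatory is claimed from them. Here the protocol makes significance on them part of what the trial sets out to show, applies one threshold to everything, and leaves open what would count as success.

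A report could therefore pick out whichever secondary outcome fell below 0.05 in favour of laser and present it as confirming the hypothesis. The trial is unblinded, and pain and satisfaction are reported by the patient, so a selective claim of this kind deserves a guard in the text. The chance of such a claim when nothing differs is higher than the threshold in 8.2 suggests.

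**Working it through.** **The plan's own figure.** The protocol gives no error rate for the secondary outcomes. The only operating figure it states is the power for the primary outcome in section 7.4: 80.2% with 95 per arm, medians of 8 and 13.5 days, 14 days of observation and two-sided 0.05. Assuming exponential recovery times:

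- Hazard ratio: 8/13.5 = 0.593.
- Probability of recovery by day 14: 1 − 0.5^(14/8) = 0.703 (laser) and 1 − 0.5^(14/13.5) = 0.513 (classic).
- Expected events: 95 × (0.703 + 0.513) = 115.5.
- Power (Schoenfeld): Φ(|ln 0.593| × √(115.5/4) − 1.96) = 80.3%.

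This agrees with the protocol. It also shows that the primary comparison is a single test with its own 0.05, separate from what follows.

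**Inputs for the secondary outcomes.**

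- Threshold: two-sided 0.05 (8.2). Because section 3 says better, only results favouring laser count, which is 0.025 per test.
- Number of tests k: 10 (without the second follow-up study) to 13 (all items), one test per outcome (3.1.2).
- Assumption: one significant outcome is enough. The protocol does not say this.
- Assumption for the base case: independent tests and no true difference.

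**At least one result favouring laser, 1 − 0.975^k.**

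- k = 10: 1 − 0.776 = 22.4%
- k = 11: 24.3%
- k = 13: 1 − 0.720 = 28.0%

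Against 2.5% for one outcome, this is 9 times (22.4/2.5) to 11 times (28.0/2.5) as high.

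**At least one result in either direction, 1 − 0.95^k.**

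- k = 10: 40.1%
- k = 13: 48.7%

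**Effect of correlation.** Simulation with equally correlated normal test statistics (400,000 draws); the correlations are assumed. At least one result favouring laser:

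| Correlation | k = 10 | k = 13 |
|---|---|---|
| 0.3 | 17.9% | 21.3% |
| 0.5 | 14.3% | 16.7% |

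**Effect of the success rule.** If two outcomes favouring laser were required, under independence the chance is 1 − 0.975^k − k × 0.025 × 0.975^(k−1):

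- k = 10: 1 − 0.7763 − 0.1991 = 2.5%
- k = 13: 1 − 0.7195 − 0.2399 = 4.1%

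The result depends far more on the unstated success rule than on the exact count of outcomes.

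**The case against.** **No rule says that one result suffices.** This stands. Section 3 uses the plural and 8.2 sets no number, so the 22% to 28% rests on a reading. The opposite reading, that every secondary outcome must be significantly better, would not inflate error, but it sits badly with the rest of the protocol. Section 3 claims only that effectiveness stays within 30%, yet presence of the complaint is itself a secondary outcome. Section 7.9 calls the infection risk similar in the two arms, and the Summary gives wound infection as 3.4% for laser and about 2% for classic surgery. What remains is an unspecified some.

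**The count may be too high.** This stands in part. For cost-effectiveness and budget impact 8.2 names no specific test; without them k is 10 or 11. If better covered only pain, complications, satisfaction and return to work, k would be 4 and the chance 1 − 0.975^4 = 9.6%. The protocol does not draw that line.

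**Multiplicity belongs in the SAP.** Section 8.2 does not use the word unadjusted, and a SAP not shown here could add a procedure. The point, however, is what the protocol itself states: a hypothesis that includes secondary significance, and a 0.05 criterion with no limit on its scope. A SAP would have to narrow both.

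**Stronger readings that the documents do not support.**

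- A reader might infer that the clause is met by chance in about half of trials with no difference. The 40% to 49% includes results where laser is significantly worse, and these do not meet a claim of better.
- A reader might multiply 10 outcomes by three later visits and reach 1 − 0.95^30 = 79%. The protocol does not say that every outcome is tested at every visit; some, such as return to work, are not repeated measures. Visits in the same patients are not independent, and the figure again counts both directions. Repeated testing would raise the chance, but the protocol does not allow this to be sized.
- A reader might say that the claim cannot be refuted. Even if one result suffices, 72% to 78% of trials with no difference (independent tests, k = 13 to 10) would show no significant outcome favouring laser.

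**Conclusion.** The point holds as a fault in how the hypothesis and the significance criterion fit together. Section 3 makes a confirmatory statement about secondary outcomes that it does not define, and 8.2 gives every analysis the same threshold.

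Assuming that one significant outcome is enough, the chance of at least one favouring laser with no true difference is about 22% to 28% for 10 to 13 independent tests, and about 14% to 21% with an assumed correlation of 0.3 to 0.5. The reference is 2.5% for a single outcome. If two were required, it would be about 2.5% to 4% under independence.

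A reader might infer that the trial's main conclusion is compromised. It is not: recovery time is a single primary outcome with its own test, its 5% error rate is unaffected, and nothing in the protocol makes that conclusion depend on the secondary outcomes. The matter is worth correcting because the remedy is cheap and stops a chance finding from being reported as confirming the hypothesis.

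**What to change.** In 8.2, limit the confirmatory 0.05 criterion to the primary outcome. State that secondary outcomes will be reported as differences with 95% confidence intervals and labelled supportive or exploratory.

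If a confirmatory claim on secondary outcomes is wanted, name a few of them with one time point each and apply Holm's procedure across them.

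Reword the last clause of the hypothesis in section 3 to match whichever course is chosen.

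The cost is about two sentences of protocol text and no new data. The downside is that isolated nominal results can no longer be presented as confirming the hypothesis.
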